### 6.3.1 Dose Modifications for panitumumab

#### 6.3.1.1 Interruption of panitumumab infusion

Subjects who experience any serious infusion reaction during panitumumab administration will have the infusion stopped. Continuation of dosing will be based on the severity and resolution of the event and will be at the discretion of the investigator.

Suspected infusion reactions should be reported as an adverse event. All subjects who experience such an event will be followed for safety.

#### 6.3.1.2 Panitumumab dosage adjustments

For subjects who experience toxicities while on study, one or more doses of panitumumab may need to be withheld, reduced, or delayed (administered at > 14 day intervals). On resolution of toxicity, a limited number of attempts to re-escalate reduced panitumumab doses will be allowed (outlined in Figure 2). Dose escalations above 6 mg/kg starting dose are not allowed. Panitumumab dose reductions are listed in Table 1.

**Table 1: Panitumumab dose reductions**

|                | Starting dose | 1 st dose reduction | 2 nd dose reduction |
|----------------|---------------|--------------------------------|--------------------------------|
| Percentage (%) | 100           | 80                             | 60                             |
| mg/kg          | 6             | 4.8                            | 3.6                            |

**Figure 2: Panitumumab dose modification algorithm for toxicity**[figure not shown]

\* Assess toxicity before each cycle. Toxicity recurs = meets the criteria for withholding a dose of panitumumab at any time during the study (see Section 6.3.1.3)

♦ Assess toxicity before each cycle. Toxicity resolved = meets the criteria for restarting panitumumab (see section 6.3.1.4). Subjects from whom > 2 subsequent cycles of panitumumab are required to be withheld should not be re-treated with panitumumab.

‡ Up to 2 subsequent doses of panitumumab may be withheld but panitumumab may not be withheld longer than 6 weeks from the previous dose. The second dose should only be withheld if the toxicity has not resolved by the time that the subsequent cycle of chemotherapy is due.

### 6.3.1.3 Criteria for withholding a dose of panitumumab

#### Skin- or nail-related toxicities:

- Symptomatic skin- or nail-related toxicity requiring narcotics, systemic steroids, or felt to be intolerable by the subject
- Skin or nail infection requiring IV antibiotic or IV antifungal treatment
- Need for surgical debridement
- Any skin- or nail-related serious adverse event

An algorithm for managing specific panitumumab-related adverse events is shown in Figure 2.

#### Non-skin- or nail-related toxicities:

- Any grade 3 or 4 toxicity with the following exceptions:
  - Panitumumab will only be withheld for symptomatic hypomagnesemia and/or hypocalcemia that persists despite aggressive magnesium and/or calcium replacement
  - Panitumumab will only be withheld for grade 3 or 4 nausea, diarrhea, or vomiting that persists despite maximum supportive care
  - Panitumumab will only be withheld for grade  $\geq 3$  anemia or grade 4 thrombocytopenia that cannot be managed by transfusion(s) or cytokine therapy

### 6.3.1.4 Criteria for re-treatment with panitumumab

Panitumumab may be restarted once:

#### Skin- or nail-related toxicities:

- The adverse event has improved to  $\leq$  grade 2 or returned to baseline or
- The subject has recovered to the point where symptomatic skin- or nail-related toxicity is felt to be tolerable or
- Systemic steroids are no longer required or
- IV antibiotic or IV antifungal treatment is no longer required

Non-skin or nail-related toxicities: Panitumumab administration may be restarted once the adverse event has improved to  $\leq$  Grade 1 or returned to baseline.

### 6.3.1.5 Dose modification schedule

Subjects should be assessed for toxicity before each dose. Dose modification should be performed according to the schedule described below and outlined in Figure 2.

Subjects who develop a toxicity that does not meet the criteria for withholding a dose of panitumumab (Section 6.3.1.3) should continue to receive panitumumab and their symptoms should be treated.

Panitumumab-related toxicity will be considered resolved if it improves to a degree that allows for re-treatment with panitumumab (Section 6.3.1.4).

For subjects who experience a toxicity that meets the criteria for withholding a dose of panitumumab:

- Subjects receiving either 100% or 80% of the starting dose of panitumumab are allowed to have up to 2 subsequent doses withheld for toxicity. However, a second dose should only be withheld if the toxicity has not resolved by the time that the subsequent cycle of chemotherapy is due.
- Subjects treated at the 100% dose level whose toxicity resolves after 1 dose of panitumumab is withheld should be re-started at the 100% dose level (recommended but not required, reduction to the 80% dose is allowed as an alternative to re-challenge with the 100% dose).
- If toxicity recurs, subjects treated at the 100% dose or 80% dose should be re-started at the 80% dose or 60% dose, respectively, when the toxicity resolves after withholding 1 or 2 doses of panitumumab.
- Subjects treated at the 100% dose level whose toxicity resolves only after 2 subsequent doses of panitumumab are withheld should be re-started at the 80% dose level.
- Subjects treated at the 80% dose level whose toxicity resolves after withholding 1 or 2 doses of panitumumab should be re-started at the 60% dose level.
- Subjects who experience toxicity at the 60% dose level will not be re-treated with panitumumab.

It is recommended that panitumumab doses will be escalated in subjects whose toxicity resolves to the degree that meets the criteria for re-starting a dose of panitumumab (Section 6.3.1.4). Dose escalations are recommended but not required. Dose escalations should occur in the following manner:

- Subjects treated at the 80% dose level whose toxicity does not recur should receive the 100% dose level at the next cycle unless a previous attempt to re-escalate to the 100% dose level was not tolerated (re-initiation of the 80% dose is allowed as an alternative to dose escalation).

- Subjects treated at the 60% dose level whose toxicity does not recur should receive the 80% dose at the next dose unless a previous attempt to re-escalate to the 80% dose level was not tolerated (re-initiation of the 60% dose is allowed as an alternative to dose escalation).

**Subjects who must have a delay of panitumumab administration beyond 6 weeks from the previous dose of panitumumab (i.e., 3 or more consecutively missed doses) due to toxicity, will be considered unable to tolerate panitumumab and will not be re-treated with panitumumab. Nevertheless, those patients will remain in the study and chemotherapy without panitumumab is continued as scheduled.**

If a subject demonstrates a clinical benefit with a demonstrated response of stable disease, partial response or complete response and there are reasons that the above dose modification rules cannot be implemented, the investigator should contact and discuss the reasons with the sponsor. The investigator must obtain written agreement from the sponsor before any changes in the dose modification rules can be implemented.

#### **6.3.1.6 Panitumumab delayed or missed doses**

Panitumumab should be given on the first day of each chemotherapy cycle. Delays of panitumumab administration beyond 6 weeks from the previous dose of panitumumab are not allowed.

Reasons to withhold a dose of panitumumab are described in Section 6.3.1.3. If a subject is able to receive a cycle of FOLFOX but panitumumab must be withheld due to toxicity, FOLFOX should be administered, and this dose of panitumumab will be considered missed. For all subjects, delays of panitumumab beyond 6 weeks from the previous dose of panitumumab (i.e., 3 or more consecutive missed doses) are not allowed and panitumumab therapy will be permanently discontinued. Missed panitumumab doses will not be made up.

### **6.3.2 Dose Modifications for chemotherapy**

#### **6.3.2.1 General aspects**

If severe hematological or non-hematological toxicity should occur, the dose modifications provided in Table 2 are recommended for the subsequent cycle. Please refer to section 6.4 for general pre-conditions for the start of a new cycle. A treatment delay of one component of the chemotherapy regimen (i.e. oxaliplatin, 5-FU) results in a delay of the other component to allow both therapies to be given together on day 1 of each 2-week cycle.

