### 6.3 Dose Modifications

Toxicity will be graded according to NCI-CTCAE, version 4.03; the therapy modifications described below are applied according to this severity grading.

Toxicities of severity grade 1 only will not lead to any dose reduction or cycle delay. The same holds for adverse reactions without any potential of serious or life-threatening complications according to the judgment of the physician (e.g., alopecia). Presumably, severe overlapping toxicity between chemotherapy and antibody will not occur (except for diarrhea). Thus, in case of toxicity requiring treatment modification, this alteration should reflect the causal relationship of the respective drug(s). E.g., if the toxicity is unequivocally caused by only one drug, a dosage modification of the other drugs is not required. Likewise, a delay of chemotherapy or the antibody does not lead to the delay of the other modality.

If more than one different type of toxicity occurs concurrently, the most severe grade will determine the modification.

In case of a necessary dose reduction the lower dose level will be applied throughout the rest of the therapy without re-escalation (except for panitumumab, see section 6.3.1). If toxicity requires a treatment delay of more than 3 weeks after the last regularly scheduled dosing date (i.e., 5 weeks after last regular treatment with **all** treatment components), study treatment continuation should be evaluated carefully by the investigator.

In case of acute allergic reactions of grade 3 or 4, the respective agent should be discontinued permanently; in case of grade 1 or 2, it is up to the physician to continue treatment without dose modification and using pre-treatment IV antihistamines and corticosteroids, if this is in the best interest of the patient.

Each dose modification or treatment delay has to be documented in the CRF, including the respective reason.

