**Table 2: Chemotherapy dose modification in case of hematological or non-hematological toxicity**

| CTC grade                          | Percent of initial chemotherapy dose |
|------------------------------------|--------------------------------------|
| 0 - 2                              | 100%                                 |
| 3 - 4                              | 75%                                  |
| 3 - 4 (2 nd occurrence) | 50%                                  |

If a grade 3 or 4 toxicity occurs after two dose reductions, the patient is taken off treatment. If the pre-conditions for the start of a new course (according to section 6.4) are not met, treatment should be delayed up to a maximum of 3 weeks.

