### 6.3.2.2 Specific toxicities - hematologic toxicities

In the event of any pre-cycle hematology profile identifying neutropenia and or thrombocytopenia, treatment should be delayed until the absolute neutrophil count (ANC)  $\geq 1.5 \times 10^9/L$ , platelet count  $\geq 75 \times 10^9/L$ , and recovery from non-hematological toxicity to baseline or grade  $\leq 1$ . Treatment should then be re-initiated with the doses indicated in Table 3, Table 4, and Table 5.

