**Table 3: Modification of FOLFOX due to NEUTROPENIA**

| CTC grade                  | Grade 2                             | Grade 3                                                                                                                   | Grade 4                                                                |
|----------------------------|-------------------------------------|---------------------------------------------------------------------------------------------------------------------------|------------------------------------------------------------------------|
| ANC                        | $\geq 1.0$ to $< 1.5 \times 10^9/L$ | $\geq 0.5$ to $< 1.0 \times 10^9/L$                                                                                       | $< 0.5 \times 10^9/L$                                                  |
| 1 st occurrence | No dose adjustment                  | Cytotoxic drugs at 75% of initial dose.
Consider prophylactic G-CSF                                                    | Cytotoxic drugs at 50% of initial dose.
Consider prophylactic G-CSF |
| 2 nd occurrence | No dose adjustment                  | Cytotoxic drugs at 50% of initial dose.
Consider prophylactic G-CSF                                                    | Stop treatment permanently                                             |
| 3 rd occurrence | No dose adjustment                  | Stop treatment permanently unless it is in the subject's best interest to continue on 5-FU/leucovorin alone + panitumumab | Not applicable                                                         |

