**Table 4: Modifications of FOLFOX due to FEBRILE NEUTROPENIA**

| CTC grade   | Grade 2               | Grade 3               |
|-------------|-----------------------|-----------------------|
| ANC         | $< 1.0 \times 10^9/L$ | $< 1.0 \times 10^9/L$ |
| Temperature | $\geq 38.5^\circ C$   | $\geq 38.5^\circ C$   |

| Life-threatening sepsis    | No                                                                                                                                                     | Yes                                                                                                                                                    |
|----------------------------|--------------------------------------------------------------------------------------------------------------------------------------------------------|--------------------------------------------------------------------------------------------------------------------------------------------------------|
| 1 st occurrence | Cytotoxic drugs at 75% of initial dose. Consider prophylactic G-CSF                                                                                    | Stop treatment permanently unless it is in the subject's best interest to continue on 5-FU/leucovorin alone + panitumumab. Consider prophylactic G-CSF |
| 2 nd occurrence | Stop treatment permanently unless it is in the subject's best interest to continue on 5-FU/leucovorin alone + panitumumab. Consider prophylactic G-CSF | Stop treatment permanently                                                                                                                             |

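### Tables 2 to 5 give different chemotherapy doses, or stop versus continue, for the same blood count, and the protocol does not say which table prevails

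*Protocol*

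**What the plan says.** Section 6.3.2.1 (General aspects) introduces Table 2 with "If severe hematological or non-hematological toxicity should occur, the dose modifications provided in Table 2 are recommended for the subsequent cycle". The table is titled "Chemotherapy dose modification in case of hematological or non-hematological toxicity", so blood counts are within its scope. It treats grades 3 and 4 alike: 75% at the first occurrence and 50% at the second. The text beneath it adds: "If a grade 3 or 4 toxicity occurs after two dose reductions, the patient is taken off treatment".

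Section 6.3.2.2 (Specific toxicities – hematologic toxicities) covers neutropenia and thrombocytopenia found in the pre-cycle blood count. Once counts have recovered, it instructs: "Treatment should then be re-initiated with the doses indicated in Table 3, Table 4, and Table 5". For a first grade 4 neutropenia (ANC below 0.5 × 10⁹/L), Table 3 says "Cytotoxic drugs at 50% of initial dose. Consider prophylactic G-CSF"; for a second, it orders a permanent stop. Table 4 covers fever with ANC below 1.0 × 10⁹/L. It separates its two columns by the row "Life-threatening sepsis" and labels them grade 2 (no) and grade 3 (yes). Table 5 is set out by platelet range and carries no grades.

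Section 6.3 has a rule for simultaneous toxicities: "If more than one different type of toxicity occurs concurrently, the most severe grade will determine the modification". It also says that a reduced chemotherapy dose is kept for the rest of therapy; only panitumumab may be re-escalated.

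**The concern.** A site facing a very low neutrophil or platelet count can find two tables that fit the event and give different instructions. Sometimes the difference is one of dose, sometimes of stopping or continuing. Because chemotherapy is not re-escalated, the table chosen at the first event fixes the dose that follows. Table 4's grade labels make this harder: the same ANC carries a lower grade there than in Table 3, while section 6.3 ranks simultaneous toxicities by grade. What is at stake is patient safety and uniform conduct across about 95 centers.

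**Working it through.** **Inputs.** Tables 2 to 5 (sections 6.3.2.1 and 6.3.2.2), the simultaneous-toxicity and no-re-escalation rules (section 6.3), and starting doses of 2400 mg/m² 5-FU and 85 mg/m² oxaliplatin (section 3.1). Counts are × 10⁹/L. A qualified stop means stop, unless continuing on 5-FU/leucovorin with panitumumab is judged best for the patient. The protocol gives no figure to reproduce here, so the check sets the tables side by side.

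**Step 1: Table 2 against Tables 3 and 5**

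| Count | Occurrence | Table 2 | Table 3 or 5 | Agree? |
|---|---|---|---|---|
| ANC 0.5 to <1.0 (grade 3) | 1st | 75% | 75% | yes |
| | 2nd | 50% | 50% | yes |
| | 3rd | off treatment | qualified stop | no |
| ANC <0.5 (grade 4) | 1st | 75% | 50% | no |
| | 2nd | 50% | permanent stop | no |
| Platelets <25 | 1st | 75% | 50% | no |
| | 2nd | 50% | qualified stop | no |

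The platelet rows rest on an inference. Table 5 has no grades, so treating platelets below 25 as grade 4 is read from its bands and from section 6.4, which ties platelets above 75,000/µL to the absence of grade 2 or worse toxicity.

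**Step 2: size of the difference at a first ANC below 0.5**

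- 5-FU: 0.75 × 2400 = 1800 mg/m² (Table 2); 0.50 × 2400 = 1200 mg/m² (Table 3).
- Oxaliplatin: 0.75 × 85 = 63.75 mg/m²; 0.50 × 85 = 42.5 mg/m².
- Ratio: 1800 / 1200 = 1.5.

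**Step 3: Table 3 against Table 4 when there is fever**

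The last column applies the most-severe-grade rule, on the supposition that neutropenia and febrile neutropenia count as different types of toxicity.

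| ANC | Life-threatening sepsis | Occurrence | Table 3 | Table 4 | Result under the rule |
|---|---|---|---|---|---|
| 0.5 to <1.0 | no | 1st | grade 3: 75% | grade 2: 75% | 75%, tables agree |
| 0.5 to <1.0 | no | 2nd | grade 3: 50% | grade 2: qualified stop | 50% |
| <0.5 | no | 1st | grade 4: 50% | grade 2: 75% | 50% |
| <0.5 | no | 2nd | grade 4: stop | grade 2: qualified stop | stop |
| 0.5 to <1.0 | yes | 1st | grade 3: 75% | grade 3: qualified stop | tie, undecided |
| 0.5 to <1.0 | yes | 2nd | grade 3: 50% | grade 3: stop | tie, undecided |
| <0.5 | yes | 1st | grade 4: 50% | grade 3: qualified stop | 50%; the qualified stop is displaced |
| <0.5 | yes | 2nd | grade 4: stop | grade 3: stop | stop, tables agree |

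If the rule applies, it settles the non-septic conflicts in favor of Table 3. In the four septic combinations it displaces Table 4's qualified stop once, ties twice and meets agreement once. If the rule does not apply, because the two are one event, the displacement disappears, but every disagreement between Tables 3 and 4 stays open.

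**The case against.** The strongest reply is structural. Table 2 sits under a general heading and is only recommended; Tables 3 to 6 sit under headings for specific toxicities. Table 6 follows the same pattern: it stops oxaliplatin for some grade 3 neurotoxicity where Table 2 would give 75%. Read as a general default with specific exceptions, much of Step 1 resolves. This has weight and is probably how many sites would read the section. But Table 2 names hematological toxicity in both its title and its introduction, no sentence gives way to the specific tables, and the headings cannot rank Table 3 against Table 4, since both stand in 6.3.2.2.

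A second reply is that Tables 3 to 5 are tied to the pre-cycle count. That would let the same ANC lead to different doses depending on the day of sampling. Section 6.2.2.2 places the white-cell nadir at days 9–14 of a 14-day cycle, so a low count may appear before or at the pre-cycle draw.

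Three stronger readings are tempting and are not supported:

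- A reader might infer that the most-severe-grade rule overrides the stop instruction in life-threatening neutropenic sepsis generally. It does so in one of four septic combinations, a first episode with ANC below 0.5, and only if neutropenia and febrile neutropenia count as different toxicities, which the protocol does not say. The instruction displaced is itself a qualified stop.
- A reader might infer that febrile neutropenia labeled grade 2 would drop out of the grade III/IV/V safety tables of section 8.4.4. Section 7.4 requires adverse events to be graded by NCI-CTCAE 4.03, and nothing tells sites to record grades from a dosing table.
- A reader might infer bias in the progression-free survival comparison. None is shown. Tables 3 to 5 are titled as FOLFOX modifications, and a reduction carried over from induction precedes randomization, so it would be expected to balance between the arms.

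**Conclusion.** The inconsistency is real. At ANC below 0.5, Tables 2 and 3 differ at both the first and the second occurrence: a 1.5-fold difference in dose, then continuing versus permanent stop. Tables 2 and 5 differ in a similar way for platelets below 25, if that range is taken as grade 4. Tables 3 and 4 disagree for fever without life-threatening sepsis at ANC below 0.5 (first occurrence, 50% versus 75%) and at ANC 0.5 to below 1.0 (second occurrence, 50% versus a qualified stop). Table 4's grade labels do not match Table 3's, so the rule in section 6.3 either favors Table 3 or leaves a tie, depending on a point that the protocol does not settle.

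The ANC findings need no assumption beyond reading the tables as written. The number of patients affected cannot be derived, because the protocol gives no rate of grade 4 neutropenia; the point does not depend on one. It concerns safety and uniform conduct, not the validity of the randomized comparison.

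**What to change.** Reconcile section 6.3 with sections 6.3.2.1 and 6.3.2.2, including Tables 2 to 5:

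- State how Table 2 ranks against Tables 3 to 5, either by limiting it to toxicities without a table of their own or by making its hematological entries agree with theirs.
- State how Table 3 ranks against Table 4 when a patient has both a low ANC and fever.
- Align Table 4's grade labels with Table 3 and with the NCI-CTCAE 4.03 grading that the protocol prescribes, and add grades to Table 5.
- State whether neutropenia and febrile neutropenia are one toxicity or two for the most-severe-grade rule, and what happens when grades tie.

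Which doses and stop rules stand is for the sponsor's clinical team. The cost is protocol wording, made by amendment under section 12, and a letter to sites. It needs no additional patients, visits or staff.

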**Table 2: Chemotherapy dose modification in case of hematological or non-hematological toxicity**

| CTC grade                          | Percent of initial chemotherapy dose |
|------------------------------------|--------------------------------------|
| 0 - 2                              | 100%                                 |
| 3 - 4                              | 75%                                  |
| 3 - 4 (2 nd occurrence) | 50%                                  |

If a grade 3 or 4 toxicity occurs after two dose reductions, the patient is taken off treatment. If the pre-conditions for the start of a new course (according to section 6.4) are not met, treatment should be delayed up to a maximum of 3 weeks.

